## Assignment of interventions

### Sequence generation, randomisation, and allocation

Eligible participants who provide written, informed consent will be randomised on a 1:1 basis to one of two trial arms. Prior blocked randomisation list with 75 sets of numbers will be generated using the Research Randomizer and kept in sealed envelopes. As soon as the consent form is received, the RTM will sequentially open the sealed envelopes containing the paper with the number assignment and unfold it. The number written specifies the group to which the adult burn survivor will be allocated. The allocation sequence will be concealed to RN-1 and the research assistant (RA) to minimise bias in the study.

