**Methods:**

A single-centre, double-arm randomised controlled trial with a process evaluation phase will be utilised for this study. All adult burn survivors aged ≥ 18 years with burn size ≥ 10% total burn surface area at the site during the study period will be screened for eligibility at least 72 h to discharge. A sample size of 150 will be block randomised to treatment (receiving the nurse-led transitional care programme and routine post-discharge service) and control groups (receiving routine post-discharge service). The nurse-led transitional care programme comprises of predischarge and follow-up phases with the delivery of bundle of holistic interventions lasting for 8 weeks. There are three timelines for data collection: baseline, immediate post intervention, and 4 weeks post-intervention.

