### Sampling and sample size estimation

Subjects will include adult burn survivors with burn size ≥ 10% TBSA from the Burn Unit. Upon recruitment, randomisation to either control or treatment group (ratio 1:1) with a blinded approach will be carried out. For the pilot phase of the project, the pilot feasibility sample size rule suggested by Whitehead, Julius, Cooper, & Campbell will be used [50]. The rule specifies that a total sample size of 25 participants per arm. Considering possible attrition rate of 20% that has been reported in burn care literature implies that an additional 5 participants will be added to both arms summing up to 30 participants per arm (total = 60 participants).

For the main trial, the sample size calculation based on the primary outcome measure (Burn Specific Health Scale) at 95% confidence level, 90% statistical power and moderate effect size will yield a total of 38 participants per arm [51–53]. Considering an attrition rate of 20%, the final sample size will be 45 participants per arm (total = 90 participants). In all, 150 participants will be recruited for the entire study. For the follow-up process evaluation phase, we will conveniently recruit up to fifteen [15] participants from each arm whilst being guided by the principle of data saturation in addition to the burn care nurses delivering the intervention to complete the qualitative strand. Data saturation will be determined at the point where no new data emerges. The quantitative strand will include review of the recruitment, enrolment, and follow-up records.

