### Recruitment

A research nurse at the study site will identify potential subjects’ eligibility for enrolment in the study based on the inclusion and exclusion criteria described above. All participants will be enrolled/recruited by a Registered Nurse (RN-1) who will not be involved in the delivery of the intervention or outcome assessment (see Fig. 3). RN-1 will follow-up on patient’s case notes on daily basis to ascertain if any adult burn survivor has a pending discharge status. If pending discharge is noted, RN-1 will check if the adult burn survivor fulfils the criteria for inclusion; if so, the patient will be invited to participate. Details of the study will be made known and information sheet duly explained. Thereafter, RN-1 will ensure that two consent forms (covering both outcome and process evaluation phases) are signed or thumb printed by the adult burn survivor which will then be forwarded to a research assistant (RA) who will complete the baseline assessment. A research team member (RTM) who is not involved in clinical services and have no knowledge about the potential subjects will take over from this phase and proceed to work on randomisation and allocation. The subjects allocated to the intervention arm will be referred to the nurse case manager to commence the intervention. Following the exit of participants from the intervention, they will be contacted and invited to participate in the process evaluation phase.

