### Blinding

Following recruitment, any possible identifying material that could indicate to the blinded assessors, which group a participant was allocated to, will be removed. Participants will not be blinded as to the group they have been assigned to. Additionally, it will not be possible to blind the interventionists, that is, the burn care nurses who will deliver the intervention only to participants in the treatment group.

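### If the 75 sets are the blocks for 150 participants, every block has size two, and the second allocation of each pair can be deduced from the first

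*Protocol article*

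**What the plan says.** Under Sequence generation, randomisation, and allocation, the protocol article says: "Prior blocked randomisation list with 75 sets of numbers will be generated using the Research Randomizer and kept in sealed envelopes". The same section sets the ratio: "Eligible participants who provide written, informed consent will be randomised on a 1:1 basis to one of two trial arms". A research team member opens the envelopes in order, and the sequence is hidden from the recruiting nurse (RN-1) and the research assistant.

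The total appears twice. The Abstract (Methods) says "A sample size of 150 will be block randomised to treatment", and Sampling and sample size estimation says "In all, 150 participants will be recruited for the entire study". That section builds the total from a pilot, "summing up to 30 participants per arm (total = 60 participants"), and a main trial, "the final sample size will be 45 participants per arm (total = 90 participants").

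On masking, Blinding says: "Participants will not be blinded as to the group they have been assigned to". The nurses who deliver the programme are also unblinded; outcome assessors are blinded. Table 3 places the pre-discharge part of the programme in the Burn Unit, face to face. Under Recruitment, "RN-1 will follow-up on patient’s case notes on daily basis to ascertain if any adult burn survivor has a pending discharge status"; eligible patients are then invited. No block size, variation of block size or stratification is stated.

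**The concern.** Blocking keeps the arms balanced, but near the end of a block the next allocation becomes predictable to anyone who knows the earlier ones. The smaller the block, the worse this is, and two is the smallest possible block in a 1:1 two-arm trial. Here earlier allocations may be visible: there is one unit, the arms differ openly, and treatment starts on the ward before discharge. Concealing the list does not help if the next entry follows from the last one seen.

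At stake is selection bias at entry. If a person involved in inviting patients or seeking consent can foresee the arm, knowledge of the patient's prognosis or likely cooperation can influence who is enrolled and when. The resulting imbalance cannot be fully repaired in the analysis.

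**Working it through.** **Inputs.** Sets in the list: 75 (Sequence generation). Ratio 1:1, two arms (same section). Pilot 60 and main trial 90 (Sampling and sample size estimation).

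**The plan's total.** 2 × 30 + 2 × 45 = 60 + 90 = 150. This reproduces the stated 150.

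**Block size.** 150 / 75 = 2 participants per set on average. A balanced 1:1 block has even size of at least 2, so 75 blocks hold at least 75 × 2 = 150 allocations. They hold exactly 150 only if every block has size 2, which leaves no room for varied sizes.

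**Blocks of two.** The sequences are AB and BA. The second entry always follows from the first, so 1 of 2 is determined: 75 of 150 (50%). Guessing the arm that is behind in the block, and tossing a coin when level, gives 0.5 + 1 = 1.5 correct of 2. That is 75%, or 112.5 of 150.

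**Fixed blocks of four.** There are six equally likely sequences.
- AABB and BBAA: the last two entries are determined; correct guesses 0.5 + 0 + 1 + 1 = 2.5.
- The other four: only the last entry is determined; correct guesses 0.5 + 1 + 0.5 + 1 = 3.
- Determined: (2 × 2 + 4 × 1) / 6 = 1.333 of 4 = 33.3%, or 50 of 150.
- Correct: (2 × 2.5 + 4 × 3) / 6 = 2.833 of 4 = 70.8%.

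**Other schemes.** Fixed blocks of six were enumerated in the same way. Mixed sizes were simulated (20,000 lists of 150, sizes equally likely, guessing the arm that is behind).

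| Scheme | Determined | Guessed correctly |
|---|---|---|
| Fixed 2 | 50.0% | 75.0% |
| Fixed 4 | 33.3% | 70.8% |
| Fixed 6 | 25.0% | 68.3% |
| Random 4/6/8 | not calculated | 68.0% |
| Simple randomisation | 0% | 50% |

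The percentages for blocked lists are ceilings. They assume that the guesser knows every earlier allocation, and the determined share also assumes knowledge of the block size.

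**The case against.** **Block size two is not stated.** This stands. The number 75 is also the planned total per arm (30 + 45 = 75), and a list could be generated longer than needed. The per-arm reading works arithmetically but fits poorly with a blocked list made up of sets of numbers, and nothing in the text supports a surplus list. The finding must remain conditional.

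**Safeguards exist.** RN-1 neither delivers the intervention nor assesses outcomes. Under Recruitment, a team member outside clinical care takes over randomisation after consent and the baseline assessment. These measures protect the list and stand as good practice. They do not stop deduction from what is visible on the unit.

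**Stronger readings that the documents do not support.**
- A reader might infer that every second allocation is openly known in advance. It is deducible only by someone who knows the pairing, the order of enrolment and the previous allocation, and the first of each pair stays unpredictable. Nothing says that RN-1 is told past allocations. Delivery is mainly by two nurses, and other unit nurses are described as uninvolved.
- A reader might infer that RN-1 picks whom to invite and when. As written, all patients are screened and those who qualify are invited, with timing tied to discharge. Informal influence cannot be excluded, but no discretion is granted.
- A reader might infer that pairing unmasks the assessors. That would need one participant's arm, the enrolment order and the pairing. Identifying material is to be removed, and no such route is documented.

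**The gain in guessing is modest.** Also true: from 75% to about 68%. The main benefit is that the end of a block can no longer be read off with certainty when sizes vary and are withheld.

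**Conclusion.** The point holds conditionally. If the 75 sets are the blocks for the 150 participants at 1:1, the block size is two throughout. Up to 75 of 150 allocations (50%) are then determined by the one before, and 75% can be guessed. This rests on three assumptions: sets are blocks, the list covers pilot and main trial together with no surplus, and someone on the unit knows the pairing and sees the previous participant's treatment in time. The single unit and the open, face-to-face start before discharge make the third plausible; the article does not document that it happens. Selection bias is therefore a possibility that the design leaves open, not a shown defect. Because the remedy is cheap, the change should be made.

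**What to change.** For the remaining allocations, replace the 75 sets with a computer-generated list in randomly varied larger blocks, for example 4, 6 and 8, and withhold the sizes from recruiting, treating and assessing staff. Keep the existing separation of the allocator and the order of consent, baseline, then randomisation.

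Put one allocation in each envelope and say so. Implementation has the site manager sealing each list into an envelope, while Sequence generation describes a paper carrying the number that assigns one participant. If an envelope held a whole set, opening it would show both allocations of the pair, so the two sections need to be reconciled.

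If 75 means something other than the number of blocks, correct the sentence so that it no longer implies blocks of two.

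The cost is a new list and a possible final imbalance of a few participants: with a largest block of 8, a list cut off mid-block can differ by at most 8 / 2 = 4 between arms.

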### Implementation

The study team will enrol participants face to face from the burn unit of the Gansu Provincial Hospital. The doctoral student will generate the blocked randomisation list and forward it to the site manager who will then place each list in an envelope and seal them afterwards. These will be passed on to the research team member working on randomisation.

### Blinding

Following recruitment, any possible identifying material that could indicate to the blinded assessors, which group a participant was allocated to, will be removed. Participants will not be blinded as to the group they have been assigned to. Additionally, it will not be possible to blind the interventionists, that is, the burn care nurses who will deliver the intervention only to participants in the treatment group.

## Data collection, management, and analysis

### Data collection methods and management

All outcomes will be assessed at baseline (T0); that is after the patient has been recruited. Following the completion of the intervention, the second phase of data collection (T1) will be undertaken; that is at the 8th week. The third phase of data collection (T2) will be the follow-up phase at 4 weeks post-intervention. Data collection will be in the form of completion of questionnaires. The data collection process will be undertaken by three research assistants who will be blinded to the groups of the participants. The research assistants have completed a 10-h training programme covering the outcome measures to be used. Following the training, they undertook a role play to enable the research team to ascertain the inter-rater reliability/percentage agreement with the following results: Burn Specific Health Scale-B (87.7%), EQ-5D-5L (100%), HADS (92.5%), PSQI (86.7%), DASH (84.4%), VAS (100%), BPI (100%), and VSS (100%). All quantitative data will be entered and stored in SPSS Version 25 (SPSS, an IBM company, Chicago, Illinois, USA). All hard copies of documents relating to the study will be stored under lock and key only accessible to designated research team member.

For the follow-up process evaluation phase (qualitative strand), face to face semi-structured interviews with an interview guide will be utilised to collect data after the intervention period has elapsed. Topics for the interview guide will be based on the process evaluation components as highlighted in Table 1. All interview proceedings will be audiotaped and transcribed verbatim in the Trint Automated Transcription Software. Interview transcripts will be exported to QSR NVivo version 10 will be used to manage the data. All soft files related to the study will be kept in a password protected computer only accessible to the principal investigator and the doctoral student investigator. Paper files will be kept under lock and key. For the quantitative phase, we will review the recruitment, enrolment, and follow-up records.

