### Eligibility criteria

All burn survivors receiving burn care services at the study site will be screened for eligibility during the study period. Adult burn survivors aged ≥ 18 years with burn size ≥ 10% TBSA as assessed by the burn surgeon/burn care nurse (irrespective of the depth of the burn), absence of a confirmed psychiatry condition, renal failure, or diabetes mellitus and reachable on phone and WeChat will be considered for inclusion. Adult burn survivors who are unable to communicate or are enrolled in another rehabilitation trial will be excluded. Drop out will be ascertained based on participants exiting either the control or intervention before the 12th week with no intention to continue their participation. Participants for the follow-up process evaluation phase will be recruited from both arms of the trial. The intervention will be primarily provided and coordinated by two burn care nurses with referrals to other members of the multi-disciplinary burns team which comprises of burn surgeons, rehabilitation medicine specialist, and social worker/psychologist who are involved in caring for burn patients at the study site. These burn care nurses recruited to deliver the intervention will have at least 4 years working experience in the burn unit at the study site and must complete a mandatory training programme which covers contents of the comprehensive transitional care program for burn patients with theory and practice (18 h in total) and passed a competence test prior to participating in the study. Other nurses working in the same unit provide routine care to all patients and are not involved in the intervention. Since most of the nurses working in the unit are not involved with the intervention cases, the risk of contamination is minimal.

The objectives of the mandatory training programme were to enable the burn care nurses to be able to master the concept of transitional care; assess, manage, and monitor the transitional needs of burn patients using the Omaha System and make referral when applicable and demonstrate burns rehabilitation competencies (comprehensive scar, itch, and pain management; psychosocial care; aromatherapy; exercises and splinting; monitoring nutrition and hydration; and infection prevention). See Table 2 for details regarding the training programme.

**Table 2 Tab2:** Details of training programme for burn care nurses based on the TIDieR checklist

TIDieR checklist					

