Phase 1 (discharge planning/preparation): This phase will take place at least 72 h prior to the day of discharge. Guided by the Omaha System, a comprehensive patient assessment will be performed by the assigned burn care nurse based on a care plan covering environmental, physiological, psychosocial, and health-related behaviour domains will be carried out [35]. The bundle of interventions available is based on the identified need which include environmental (health education to improve sanitation and environmental hygiene within residence), physiological (pain management, itch management, comprehensive scar management, range of motion activities, management of heat sensitivity, skin care, nutritional assessment/support, infection prevention and control measures), psychosocial (social skills training, counselling care, health education, positive reinforcement, spiritual care, meditation, and music therapy), and health-related behaviour (strategies to improve sleep/rest, physical therapy, and participation in activities of daily living). See Table 3 for details regarding the bundle of intervention presented based on the TIDieR checklist.Phase 2 (follow-up phase): This phase comprises of 2 structured WeChat telehealth, 6 structured telephone follow-ups and daytime patient/family-initiated telephone service over an 8-week period. Like the discharge planning phase, care planning and intervention are undertaken using the Omaha System as a guide for the 8-week period. The bundle of interventions available based on the identified need/domain include environmental (health education to improve sanitation and environmental hygiene within residence), physiological (pain management, itch management, comprehensive scar management, range of motion activities, management of heat sensitivity, skin care, nutritional assessment/support, infection prevention and control measures), psychosocial (social skills training, counselling care, health education, positive reinforcement, spiritual care, meditation, music therapy and aromatherapy), and health-related behaviour (strategies to improve sleep/rest, physical therapy, and participation in activities of daily living). Where referrals are required, a referral form will be completed for the service to be provided. Home visits will be carried out if the adult burn survivor has concerns which can best be handled face to face by the nurse (example: assistance with wound care or reinforcing scar management education). See Table 3 for details regarding the bundle of intervention presented based on the TIDieR checklist.

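### Process-evaluation interviews may start at week 8, before the week-12 T2 assessment, because their stated trigger is the end of the intervention and not completion of T2

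*Protocol article*

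**What the plan says.** The Intervention section describes a post-discharge phase of two WeChat contacts plus "6 structured telephone follow-ups and daytime patient/family-initiated telephone service over an 8-week period". Under Data collection methods and management, T1 comes at its end: "Following the completion of the intervention, the second phase of data collection (T1) will be undertaken; that is at the 8th week". The same section then sets T2: "The third phase of data collection (T2) will be the follow-up phase at 4 weeks post-intervention".

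The timing of the process evaluation is stated twice. Recruitment gives the invitation: "Following the exit of participants from the intervention, they will be contacted and invited to participate in the process evaluation phase". Data collection methods and management gives the interview: "face to face semi-structured interviews with an interview guide will be utilised to collect data after the intervention period has elapsed". Neither sentence refers to T2.

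Interviewees come from both arms. Eligibility criteria says "Participants for the follow-up process evaluation phase will be recruited from both arms of the trial", and Sampling and sample size estimation says "we will conveniently recruit up to fifteen [15] participants from each arm whilst being guided by the principle of data saturation".

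Table 1 lists the topics. Those on recruitment and follow-up go to adult burn survivors without restriction by arm. Those on perceived against actual benefit, and on experience with clinical outcomes, go among survivors only to the intervention group. The Blinding section states that participants know their allocation.

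**The concern.** Both timing sentences refer to the end of the programme, which is not the end of outcome collection. If an interview falls between weeks 8 and 12, the participant is asked to reflect on the programme and then reports quality of life, anxiety and depression, sleep, pain, itch and function at T2.

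The benefit-focused topics go to one arm only, and the respondents know which arm they are in. Any influence on later answers therefore need not cancel between arms. It would arise after randomisation, so randomisation gives no protection against it, and analysis could not reliably remove it.

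T2 matters here. The research question covers the first 12 weeks after discharge, the primary outcome is listed at T0, T1 and T2, and T2 is the only look at whether an effect lasts once the programme stops.

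**Working it through.** **1. Timeline.** Inputs: intervention length 8 weeks (Intervention); T1 at week 8 and T2 four weeks post-intervention (Study outcomes; Data collection methods and management).

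- T2 = 8 + 4 = week 12. This reproduces the 12-week horizon in the research question and in the drop-out definition.
- Earliest interview under either timing sentence = end of intervention = week 8.
- Window in which an interview can precede T2 = 12 − 8 = 4 weeks.

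The Participant timeline section words T1 loosely, as though it came eight weeks after the intervention. I use the week-8 timing given in the other two sections.

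**2. Which assessments are exposed.** T1 falls at week 8, when the window opens, so it is largely unaffected. T2 is exposed.

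**3. Largest share of an arm that could be affected.** Input: up to 15 interviewees per arm.

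| Denominator per arm | Source | Share |
|---|---|---|
| 45 | Main trial after attrition allowance | 15/45 = 33% |
| 38 | Main trial before attrition allowance | 15/38 = 39% |
| 75 | Pilot and main trial pooled, 150/2 | 15/75 = 20% |

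The 38 row assumes that every interviewee is among the participants analysed.

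**4. What a shift would do.** The documents give no effect of an interview on later scores, so everything in this step is assumption. Let s_I and s_C be the mean shift, in SD units, among interviewed participants in the intervention and control arms. If all 15 per arm are interviewed before T2, the T2 contrast moves by

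(15/n) × (s_I − s_C).

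| Assumed shifts | n = 45 | n = 75 |
|---|---|---|
| s_I = 0.1, s_C = 0 | 0.03 SD | 0.02 SD |
| s_I = 0.3, s_C = 0 | 0.10 SD | 0.06 SD |
| s_I = 0.3, s_C = 0.15 | 0.05 SD | 0.03 SD |
| s_I = s_C (any value) | 0 | 0 |

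The first two rows are worst cases, with all 15 recruited, all seen before T2 and an effect in one arm only. A negative s_I would reverse the sign. No sample-size or power figure in the protocol depends on this.

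**The case against.** The strongest reply is that no sentence schedules an interview before T2. The wording sets an earliest date, which interviews held after week 12 also satisfy, and some of the context favours that reading:

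- The article repeatedly calls the process evaluation a follow-up phase.
- Table 1 asks about reasons for drop-out and for staying in. Drop-out is counted to week 12, so these questions can be answered fully only then.
- The drop-out definition speaks of exit from either arm before week 12. The exit that triggers the invitation could be read the same way, especially as exit from the intervention has no evident meaning for controls.
- Fig. 2 (the schedule) and Fig. 3 (the flowchart cited under Recruitment) are not available here, and either may settle the matter.

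All of this stands as a reason for caution, but none of the visible text fixes the interview date. The two explicit timing sentences both point to the end of the intervention, which the article itself puts four weeks before T2.

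It is also fair to say that the mechanism is conjectural. The interview is research data collection and nothing describes it as support. One conversation is small beside the structured contacts that the intervention arm already receives. Both arms are interviewed, and fewer than 15 per arm may take part if saturation comes early. These points limit the likely size but do not rule out a difference between arms.

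A reader might also infer that the blinded outcome assessors would hold the interviews and so learn the allocation. The documents do not support that. No passage gives them this task, and Table 1 lists the data collection team among those to be interviewed.

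**Conclusion.** The point holds as a gap in a stated rule. As worded, interviews of up to 15 participants per arm may precede T2, and part of their content is specific to the intervention group. This is conditional on Figs. 2 and 3 not placing them later.

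The exposure is limited to T2 and to at most 33% of a main-trial arm of 45, or 20% of 75 if the phases are pooled. Size and direction are unknown, and the SD figures above only illustrate worst cases.

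A reader might conclude that the T2 results will be biased in favour of the programme. The documents do not support this: they do not place any interview before T2, and they show no effect of an interview on later answers. The severity is minor.

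**What to change.** Amend the two timing sentences, under Recruitment and under Data collection methods and management, to say: *Trial participants are invited to and interviewed for the process evaluation only after their own T2 (week-12) assessment is complete, or after withdrawal has been confirmed.* This also gives controls a defined trigger and lets the drop-out questions cover the full 12 weeks. If Fig. 2 or Fig. 3 already shows interviews after T2, the edit only brings the text into line.

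The cost is two amended sentences and interviews held about four weeks later, with correspondingly longer recall of how the intervention was delivered. It needs no extra staff or participants. Interviews with nurse case managers are not affected.
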